#### European Organisation for Research and Treatment of Cancer Quality of Life Questionnaire C30

The European Organisation for Research and Treatment of Cancer Quality of Life Questionnaire C30 is a questionnaire developed to assess the quality of life of cancer patients. It is an instrument that has been translated and validated in over 90 languages and is used in more than 3000 studies worldwide.

**Table 1 table1:** Administration of study intervention and control intervention.

	Body structure and function	Activity	Questionnaires and other tests
Preoperative (3-6 weeks before surgical intervention)	Steep ramp test	Five Times Sit to Stand	International Physical Activity Questionnaire ‒ short form	
	Fatigue-Visual Analogue Scale	2-Minute Walk Test	European Organisation for Research and Treatment of Cancer Quality of Life Questionnaire C30
	Pain Numeric Rating Scale		
	Hand grip strength		
Surgical intervention	Fatigue-Visual Analogue Scale		Adherence to exercise	
	Pain Numeric Rating Scale			
	Pulse and oxygenation			
Postoperative during hospitalization	Fatigue-Visual Analogue Scale	Five Times Sit to Stand	European Organisation for Research and Treatment of Cancer Quality of Life Questionnaire C30
	Pain Numeric Rating Scale	2-Minute Walk Test	
	Hand grip strength	Modified Iowa Levels of Assistance Scale	
Postoperative (6 weeks after surgical intervention)	Steep ramp test	Five Times Sit to Stand	International Physical Activity Questionnaire ‒ short form	
	Fatigue-Visual Analogue Scale	2-Minute Walk Test	European Organisation for Research and Treatment of Cancer Quality of Life Questionnaire C30
	Pain Numeric Rating Scale		
	Hand grip strength		

#### Assessment of Postoperative Functional Recovery During Hospital Stay: Modified Iowa Levels of Assistance Scale

For assessment of postoperative functional recovery, the modified version of the Iowa Levels of Assistance Scale (MILAS) [18] will be obtained daily. The MILAS assesses the ability of patients to safely perform four activities of daily life (supine to sit, sit to stand, walking, and stair climbing) and rates the amount of assistance needed. This measurement enables the physiotherapist to assess whether and when a patient can function independently and allows tailoring treatment goals.

### Endpoints

As the primary endpoint, the complication rate will be assessed in-hospital and at the 30-day follow-up using the CCI [19,20]. Secondary endpoints are the complications assessed according to Clavien/Dindo [21], LOS, readmission rate, mortality rate, and costs as well as measures associated with physical performance. To compare the two groups and follow the progress in the intervention group, tests and questionnaires will be used (see Table 2).

### Study Procedures

Patients are allocated to our consultation center by general practitioners or gastroenterologists. They will be recruited to the study during normal consultation through senior surgeons. We will include all consecutive patients electively treated for colorectal diseases in accordance with the ERAS approach, for colorectal resections from June 13, 2016, onwards. Patients will be randomly assigned either to the control or to the intervention group after entering their data into the Web-based database. All complications will be recorded and assessed according to the Clavien-Dindo classification at the time of discharge and follow-up, by the unblinded study nurse (Table 2). Results will be transformed to the CCI score. The LOS and readmission rate will be recorded at the time of discharge and follow-up. Cost analysis will be performed with the local department of finance.

### Analyses

The statistical analysis will be performed on an intention-to-treat basis by the study’s independent statistician. For each patient, basic demographic, prehabilitation, intraoperative, postoperative, and follow-up data will be generated and stored in a password-protected and encrypted database. These data will be compared separately for each randomization group. Both significant as well as nonsignificant results will be reported accordingly.

The primary endpoint (CCI) will be compared between the two randomized groups (prehabilitation/treatment group vs no prehabilitation/control group) using the Student *t* test. The CCI is known from other trials on postoperative complications to be normally distributed [19,20].

As for the secondary outcomes, the two randomized groups will be compared with the Pearson chi-square test with regards to the Clavien/Dindo classification [21]. This is typically an ordinal variable. Furthermore, the LOS, typically with a skewed distribution, will be compared between the two randomized groups with the Mann-Whitney U test. Readmission and mortality rates will be compared with the Fisher’s exact test between the two groups. The overall total in-hospital costs between the two randomized groups will be compared either with the Student *t* or the Mann-Whitney U-test, depending on their normality of distribution. Cost-effectiveness between the two groups will be compared. All *P* values will be 2-sided and considered statistically significant, if *P*<.05. The statistical analysis will be performed on SPSS 22 for Mac.

A subgroup analysis to investigate whether disease entity (benign vs malignant disease) influences the impact of prehabilitation on the outcome will be performed. Due to the small sample size, further subgroup analysis (eg, for different procedures) will not be performed. There are no multivariable analyses planned for this study due to the nature of the study design (randomized controlled trial) as there will be no need for adjustment of the results.

An interim analysis will be performed as soon as the total sample size of the study reaches 56 patients for both groups. The purpose of the interim analysis is to assess whether the inclusion rate of patients is acceptable and as expected. Further, we analyze the possibility of unexpected rates of severe or life-threatening adverse events or the extraordinary favorable effectiveness of the intervention, which may indicate the premature closure of the trial. An ad hoc interim analysis will be performed after inclusion of 20 patients to assess practicability only.

**Table 2 table2:** Physical tests and questionnaires.

	Intervention group		Control group	
	Preoperative	Postoperative	Preoperative	Postoperative
Steep Ramp Test	x	x	x	x
Borg Rating of Perceived Exertion Scale	x	x	x	x
Numeric Rating Scale Pain	x	x	x	x
Hand grip strength	x	x	x	x
Five Times Sit to Stand test	x	x	x	x
2-Minute Walk Test	x	x	x	x
International Physical Activity Questionnaire-short form	x	x	x	x
Modified Iowa Levels of Assistance		x		x
Comprehensive Complication Index		x		x
Clavien/Dindo Score		x		x
Length of stay		x		x
Readmission		x		x
Mortality rate		x		x
Costs		x		x

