### Sample Size Calculation

The sample size calculation was performed assuming a clinically relevant 25% reduction of postoperative complications as assessed by the Comprehensive Complication Index (CCI) favoring the treatment group (prehabilitation) when compared to the control group (no prehabilitation) [7,8]. Using a dataset of 47 patients who underwent ERAS colorectal surgery in our department, we determined the mean CCI was 10 (SD 5). Thus, the treatment group mean was set at 7.5, and the standard deviation was adjusted accordingly (SD 3.75) [9]. The alpha error was typically set at .05 and power at 80%. The initial total sample size of 102 patients was increased by 10% to adjust for potential of loss to follow-up resulting in a total sample size of 112 participants (ie, 56 participants per group respectively).

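### Clavien-Dindo grade is called ordinal but is assigned a Pearson chi-square test, which ignores the order and loses power against an overall shift to milder grades

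*Protocol article*

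**What the plan says.** The Endpoints section of the protocol article makes the Comprehensive Complication Index (CCI) primary and lists Clavien-Dindo first among the secondary outcomes: "Secondary endpoints are the complications assessed according to Clavien/Dindo".

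The Analyses section sets the test for it, a Pearson "chi-square test with regards to the Clavien/Dindo classification", and comments "This is typically an ordinal variable". In the same paragraph, length of stay, described as skewed, "will be compared between the two randomized groups with the Mann-Whitney U test". All P "values will be 2-sided and considered statistically significant" below .05.

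The Study Procedures section says that complications are graded by Clavien-Dindo and that the grades are then converted into the CCI.

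The article does not say how many grade levels the chi-square table will have, whether grades will be collapsed, or what distribution is expected. The sample size and its 80% power belong to the CCI comparison only.

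**The concern.** The Pearson statistic is unchanged if the grade columns are shuffled. It asks whether the two distributions differ in any way and spreads its sensitivity over (levels − 1) degrees of freedom. The trial's hypothesis is directional: prehabilitation should reduce morbidity. The effect of interest on this scale is therefore mainly an ordered one, from higher grades towards lower grades or none. A test that uses the order puts that effect on one degree of freedom.

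This is a mismatch in the text, not something left to a later document. The article names the scale and, in the adjoining sentence, fixes a test that does not use it. At stake is a real overall shift in severity that is missed on Clavien-Dindo while the CCI, built from the same grades, points the other way.

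**Working it through.** **1. The plan's own figure.** The only sample-size calculation is for the CCI: means 10 and 7.5, SDs 5 and 3.75, two-sided alpha 0.05, power 80%.
- Root-mean-square SD = √((25 + 14.0625)/2) = 4.419.
- At 51 per arm the noncentrality is 2.5/(4.419 × √(2/51)) = 2.857, and power from the noncentral t distribution is 0.808. At 50 per arm it is 0.7997, just short of 80%.
- So 51 per arm, 102 in total, reproduces. 102 × 1.10 = 112.2, stated as 112 (56 per arm).

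These numbers fix the arm sizes used below. They give no power for Clavien-Dindo.

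**2. Cost of the extra degrees of freedom, with no grade distribution assumed.** Take a noncentrality that gives 80% power on 1 df: (1.960 + 0.842)² = 7.85. Spread over more degrees of freedom, the same noncentrality gives:

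| df | Power |
|---|---|
| 1 | 80% |
| 2 | 71% |
| 3 | 64% |
| 5 (six levels) | 56% |
| 7 (eight levels) | 49% |

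**3. Simulation with assumed distributions.** Inputs: highest grade per patient, 56 per arm, 6,000 simulated trials per scenario, 60% of controls with no complication. Assumed control proportions for six levels (0, I to V) are .60/.12/.14/.09/.03/.02. The eight-level version splits III and IV into a and b. Four levels are 0, I, II, III+; three are 0, I-II, III+. The treatment arm follows a proportional-odds shift, with the odds ratio (OR) for a worse grade below 1. Check of the shift: the control odds of no complication are .60/.40 = 1.5; at OR 0.45 they become 1.5/0.45 = 3.33, a proportion of 3.33/4.33 = .769. Entries are power, chi-square vs Mann-Whitney.

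| Levels | OR 0.60 | OR 0.45 | OR 0.35 | OR 0.25 |
|---|---|---|---|---|
| 8 | 9% vs 26% | 20% vs 50% | 35% vs 71% | 57% vs 88% |
| 6 | 12% vs 26% | 25% vs 51% | 42% vs 71% | 66% vs 89% |
| 4 | 16% vs 26% | 33% vs 51% | 53% vs 72% | 75% vs 89% |
| 3 | 19% vs 25% | 41% vs 51% | 59% vs 71% | 81% vs 88% |

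With 50% to 70% of controls free of complications at eight levels, and 50% to 60% at six, the ratio of chi-square to Mann-Whitney power was 0.29-0.74 (eight levels), 0.45-0.81 (six), 0.61-0.84 (four) and 0.76-0.92 (three). The loss is 1 minus the ratio, so it runs from 8% to 71% overall.

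A 25% relative cut in every grade, borrowing the size of effect the plan uses for the CCI, gives 6% vs 18% with eight levels, 10% vs 19% with six and 15% vs 19% with three (60% none).

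**4. Sparse cells.** The expected count in a cell is 56 times the mean proportion of the two arms. With eight levels, control proportions .50/.17/.17/.04/.06/.03/.01/.02 and no effect, grades IIIa to V give 2.24, 3.36, 1.68, 0.56 and 1.12. That is five grades in two arms, or 10 of 16 cells below 5. Across the scenarios at 56 per arm:
- eight levels: 10-14 of 16 cells below 5;
- six levels: 4-8 of 12;
- four levels: 0-2 of 8;
- three levels: none.

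At 51 per arm and OR 0.35, the collapsed tables can dip just under 5: for III+ with three levels, 51 × (.14 + .054)/2 = 4.95.

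Under no effect, the eight-level chi-square rejects in 2.4-3.3% of trials. The Mann-Whitney test stays near 5%.

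**5. A scenario that goes the other way.** Eight levels, 51 per arm, control .50/.15/.20/.05/.05/.02/.01/.02 and treatment .50/.30/.18/.01/.01/0/0/0. The share with no complication is unchanged and only severity among the rest falls. Power is about 36% for the chi-square and 16% for the Mann-Whitney test.

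**The case against.** The strongest objection concerns size. A reader might infer that the chi-square table will be mostly sparse and that more than half the power is lost. The article does not support that as a fact. It fixes neither the number of levels nor the distribution, and a condensed article may leave the tabulation to the full protocol. More than half is lost with all eight grades at small to moderate effects and is borderline with six. With three levels it does not occur, and the sparseness and conservatism largely disappear. This objection stands, and is why the cost is given as a range.

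Second, the proportional-odds model favours rank tests. If only severity among patients with complications changes, the ranking of the tests reverses (step 5). This also stands. It makes the choice a trade-off, but an overall shift that includes fewer patients with any complication is closer to the stated hypothesis of reduced complication rates.

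Third, the rank test is no rescue: at OR 0.45 its power is still only about 50%. That is correct, and the trial was not sized for this comparison.

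Three further inferences should not be drawn:
- That a significant chi-square leaves the better arm unknown. The statistic has no sign, but the grade-by-arm table shows where the arms differ.
- That using Fisher's exact test for readmission and mortality is inconsistent with the choice here. Those outcomes are binary.
- That sparse cells inflate false positives. In these simulations the test was conservative.

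Finally, the CCI already uses severity quantitatively, so an ordered comparison of morbidity exists in the plan. This limits the impact but does not remove the mismatch.

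**Conclusion.** The point holds as a mismatch between the stated scale and the stated test. Under an overall proportional-odds shift with 51 to 56 per arm, the Pearson chi-square gives up roughly 10% to 70% of the power of a rank test: most with the full eight-grade scale, least with three collapsed levels. The range rests on assumed grade distributions (50% to 70% of controls without complications), assumed odds ratios of 0.25 to 0.60, and the worst grade per patient as the unit. None of these comes from the article. The chi-square lost power in every ordered overall shift tried, but not when severity changed with the complication-free share held fixed. The primary analysis and the sample size are untouched. It should be corrected, but it does not threaten the trial's main conclusion.

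**What to change.** Replace the chi-square sentence in the Analyses section with one along these lines: the highest Clavien-Dindo grade per patient, with 0 for no complication, will be compared between groups with the Mann-Whitney U test; the grade-by-arm table will be presented descriptively. A proportional-odds model reporting a common odds ratio with 95% CI is an equally good choice and adds an effect size. State the grade levels to be used, so that any collapsing is fixed before the data are seen.

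The cost is a sentence or two, with no new data or patients; the Mann-Whitney test is already planned for length of stay. The article reports 40 of 112 patients included, so the change can precede the final analysis. The one downside is lower sensitivity to a change in severity that leaves the complication-free share unchanged; the descriptive table would still show such a pattern.

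### Early closure for benefit at 56 of 112 patients has no boundary, so the stated 5% type I error is exceeded by an uncontrolled amount (about 8.3% if P<.05 is applied)

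*Protocol article*

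**What the plan says.** All of this is in the Methods of the protocol article.

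- **Timing (Analyses):** "An interim analysis will be performed as soon as the total sample size of the study reaches 56 patients for both groups". I read this as 56 patients in total, half of the planned 112. Read as 56 per group it would be the whole trial, and there would be no interim.
- **Purpose (Analyses):** the look first checks the inclusion rate. It then considers unexpected rates of severe adverse events, or "the extraordinary favorable effectiveness of the intervention, which may indicate the premature closure of the trial". No test, threshold or spending rule is attached. A separate look at 20 patients is restricted to practicability, so it is not an efficacy look.
- **Significance rule (Analyses):** all P "values will be 2-sided and considered statistically significant" if below .05. No exception is made for the interim.
- **Design (Sample Size Calculation):** "The alpha error was typically set at .05 and power at 80"%. Nothing is set aside for an interim look.

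**The concern.** The plan allows the trial to end early because the intervention looks very effective. A stop of that kind gives the primary hypothesis a second chance of a positive result. The 5% error rate then holds only if the interim threshold is strict and the final threshold is set with it in mind. Here the interim threshold is missing, the general rule of P<.05 covers every P value, and the final test takes all of the alpha.

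Two things are at stake. The false-positive risk of the primary comparison is above the 5% that the article states, by an amount that depends on a threshold which could be chosen after the data are seen. And an early stop on a lenient threshold, with about 28 patients per arm, would tend to report too large an effect.

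**Working it through.** **Inputs.** From Sample Size Calculation: control CCI "we determined the mean CCI was 10 (SD 5"); for the other arm "the treatment group mean was set at 7.5, and the standard deviation was adjusted accordingly (SD 3.75"); two-sided alpha .05; power 80%; 102 patients before and 112 after the dropout allowance. From Analyses: Student t test, interim at 56 patients.

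**1. Reproduce the design figure.**
- Difference: 10 − 7.5 = 2.5. Common SD: √[(5² + 3.75²)/2] = 4.42.
- Noncentral t, two-sided .05: 50 per arm gives 79.97% power and 51 per arm gives 80.8%. So 51 per arm, 102 in total, as stated.
- 102 × 1.10 = 112.2, stated as 112.

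The figure reproduces as a fixed design with one look at the full .05.

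**2. Type I error with one efficacy look.** Let Z₁ and Z₂ be the interim and final test statistics. Under the null they are bivariate normal with correlation √(information fraction). With 56/112 = 0.50 the correlation is 0.707, and

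overall error = 1 − P(|Z₁| < c₁ and |Z₂| < c₂).

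| Interim P below | Final P below | Overall error |
|---|---|---|
| .05 | .05 | 8.31% |
| .01 | .05 | 5.46% |
| .005 | .05 | 5.19% |
| .001 | .05 | 5.02% |
| .003 | .049 | 5.0% |

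Simulated t tests at 28 and then 56 per arm also give 8.31% for the first row. With the pre-dropout total as denominator (56/102 = 0.55), that row is 8.14%.

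**3. What P<.05 would mean at the interim.** Take 28 evaluable patients per arm and the plan's own means and SDs.
- Standard error: 4.42 × √(2/28) = 1.18. Noncentrality: 2.5/1.18 = 2.12.
- Probability of two-sided P<.05 on 54 degrees of freedom: 55%.
- Simulated mean observed difference among those trials: about 3.3 against a true 2.5, an overstatement of about one third (3.3/2.5 = 1.32).

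**4. If the trigger counts inclusions.** The Results section reports 40 patients included and 27 finished. On that ratio, assumed to persist, 56 included would mean 56 × 27/40 ≈ 38 finished, about 19 per arm. The information fraction would be about 38/112 = 0.34. The error under P<.05 at both looks would then be about 8.8%, and the chance of crossing at the interim about 40%. The figures in step 3 would not apply.

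**The case against.** The strongest reply is that this is an omission and not an error. The article never says that the interim is judged at P<.05. The P<.05 sentence closes a list of between-group comparisons, and the interim is described afterwards with its own standard, an effect that is extraordinary and that only may point to closure. On the plan's own assumptions P<.05 at 28 per arm is more likely than not, so it can hardly be what extraordinary means. Numerical boundaries are also often left to a full protocol or SAP, which is not shown.

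Much of this stands, and it limits the claim in three ways.

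- A reader might infer that the trial's type I error is 8.3%. The document does not establish that. It is the result of applying the only written criterion to a look for which no criterion is written. A stricter reading gives a figure nearer to 5%.
- A reader might infer that the final .05 and the alpha in the sample size are themselves mistakes. They are not: with an interim threshold of P<.001 both can stay.
- A reader might infer that the look is fixed at the 56th inclusion. The wording allows that reading but does not settle it; the article speaks of inclusion in so many words only for the 20-patient look.

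What does not stand is that nothing is wrong. The article states an efficacy stop, a significance rule without exception and a single-look sample size. Together these do not hold 5%, whichever interim threshold is meant. Extraordinary is not a criterion: it leaves the threshold to be chosen with the results in view, and the error rate is then unknown.

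**Conclusion.** The concern holds in this form: early closure for benefit is allowed at half the sample without a boundary, and the rules the article does state do not keep the overall error at 5%. The excess runs from negligible (5.02% at an interim P<.001) to material (about 8.3% at P<.05), and nothing in the text fixes where it lies.

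The range assumes one efficacy look at 50% information, a final test at two-sided .05, and no boundary set in a document not shown. The 55% and the 3.3 points assume in addition 28 evaluable patients per arm, P<.05 at the interim, and the plan's own means and SDs. With 40 patients included when the article was written, the look at 56 was still ahead, so a boundary could be set before it.

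**What to change.** Add to the interim paragraph of Analyses:

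- Early closure for benefit is considered only if the comparison of CCI between groups gives two-sided P<.001 at the interim. This look is exempt from the general P<.05 rule. The final analysis stays at two-sided .05 (overall 5.02%).
- The efficacy look uses the first 56 patients in total with completed 30-day CCI. The inclusion rate and safety can still be reviewed when 56 patients have been included.

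An O'Brien-Fleming-type spending pair of about .003 at the interim and .049 at the end is an alternative and also holds 5%.

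**Cost.** One or two sentences and no extra patients. The final threshold is unchanged under the first option. Under the second, fixed-design power at 51 per arm moves from 80.8% to 80.5% (same noncentral t calculation at .049). The efficacy look comes somewhat later, because it waits for training, surgery and 30 days of follow-up. A stop at P<.001 would still overstate the effect, but it would be uncommon: the calculation in step 3, repeated at .001, gives a chance of about 10%.
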